### D. 3. STUDY PRODUCT

**D. 3. a. Active product.** We will use metronidazole vaginal gel, 0.75% MetroGel-Vaginal (3M Pharmaceuticals) in this study. Based on a Clinical Monograph from the company (55), “MetroGel-Vaginal is an effective, well-tolerated local treatment for BV. Each gram of MetroGel-Vaginal contains 7.5 mg of metronidazole, 0.8 mg of methyparaben, 0.2 mg of propyl-paraben in an exclusive hydrogel vehicle consisting of purified water, propylene glycol, carbomer 934P, sodium hydroxide (to adjust pH), and edetate disodium. The gel is buffered to a normal pH of 4.0 and is free of mineral oil. Each applicatorful delivers about 5 grams of gel and contains approximately 37.5 mg of metronidazole in solution, thus, the pharmacologic activity of metronidazole is not limited by drug dissolution.”

The product is used intravaginally either once (at bedtime) or twice a day. Both regimens have comparable efficacy (1). Clinical trials which compared intravaginal gel (5 gm BID for 5 days) vs oral metronidazole (500 mg BID for 7 days) have also shown comparable efficacy of about 84% after 11-17 days from start of therapy to 71% after 34-40 days from initiation of therapy (55). Despite its wide spread use, metronidazole is reported to be highly active and drug resistance is relatively rare (55). This is a desirable feature since we intend to use this drug intermittently for a longer period. Metro-Gel is reported to increase vaginal lactobacilli (55). We anticipate longer treatment to reduce recurrences and help to restore normal vaginal flora. It is estimated that 10%-15% of women who initially respond to therapy, relapse by one month after treatment, and 50%-70% of women develop recurrences after 3 months of initial therapy (1). Several causes have been postulated to account for these recurrences (1); for example, inability to reestablish normal *lactobacillus*-dominant protective flora, persistence of BV-causing bacteria and reinfection by a male partner.

**D. 3. b. Placebo.** The placebo will be manufactured to be similar to the active product but without the active ingredient. Identical consistency, color, smell and packaging will be maintained.

**D.3. c. Provision of MetroGel and placebo.** We have discussed this protocol with 3M Pharmaceuticals and the company has agreed to donate the treatment and the placebo for this study (see Appendix: letter from 3M Pharmaceuticals).

**D. 3. d. Adverse experience (AE) reporting.** We will record all AEs in designated forms and will grade them using standard methods. These AEs will be regularly reported to the PI.

### D. 4. STATISTICAL CONSIDERATIONS

**Primary endpoints.** a) Incidence/Prevalence of BV at cross-sectional visits; b) Portion of pregnancies lost during the first 14 weeks of gestation; c) Incidence of adverse reactions to the product (portion of subjects having adverse reactions); and d) Rates of participation in study, adherence to treatment, and subsequent dropout.

**Sample size and power.** The following design specifications will apply: number of treatment groups: 2; follow-up period: approximately one year; hypotheses will be tested using a one-sided type 1 error of  $\alpha=0.05$ . Unless stated otherwise, powers are obtained based on Fisher's exact test for comparisons of proportions in two groups using software developed by Dupont and Plummer (56).

We will recruit 1664 women of whom 832 will be HIV infected and 832 will be uninfected. In each group of women, 416 will be randomized to treatment arm and 416 to placebo arm. Based on previous experience in Malawi, losses due to dropouts and non-compliance will be less than 10% per year. Thus at least 375 women in each arm will return to each study visit during the first year.

**Specific aim 1.** Power estimates for specific aim 1 is shown in Tables 11. In previous studies from Malawi, cross sectional prevalence of BV among untreated women was 30% and that of any vaginal disturbance was 89% (24).

**Table 11. Estimated power for specific aim 1 (comparing BV at each visit during the first study year assuming at least 375 evaluable study subjects in each group).**

| Normative rate
in untreated women | Reduction from intervention |            |
|----------------------------------------------|------------------------------------|------------|
|                                              | 33%                         | 50% |
| 0.30                                         | .87                                | ~1.00      |
| 0.89                                         | ~1.00                              | ~1.00      |

Thus there will be 0.87 and almost 1.00 power to detect 33% reductions in cross sectional visit prevalence of BV (normative rate 0.30 in untreated subjects) and any vaginal flora disturbance (normative rate .89 in untreated subjects).

**Specific aim 2.** Previous reports suggest that 20%-30% of women without treatment will lose their first post-index pregnancy (27). Table 12 presents powers to detect 33% and 50% reductions in the rates of early gestational loss of this first post index pregnancy based on 300 evaluable subjects in each group (we have assumed that 80% of these women will become pregnant again). There is virtual certainty to detect 50% reductions if pregnancy loss of 30% occurs, and >90% reduction if the rate of pregnancy loss is 20%. For a 33% reduction, there is about 80% power if the rate of loss is high (30%) and limited power if the rate of pregnancy loss is low (20%).

**Table 12. Estimated power for specific aim 2 assuming 300 evaluable subjects in each group during the first year.**

| Normative rate of
pregnancy loss | Reduction from intervention |            |
|---------------------------------------------|------------------------------------|------------|
|                                             | 33%                         | 50% |
| 0.20                                        | .54                                | .91        |
| 0.30                                        | .78                                | .99        |

**Data management.** Data entry and storage will be conducted on-site. The Johns Hopkins Project in Malawi has trained staff who have performed this activity for over a decade. Each record will be double entered into the computer and records compared. No direct subject identifiers (e.g., names, addresses, etc.) will be entered into data sets. The data will be stored on secure computers in Malawi and Johns Hopkins University. All original data collection forms will be kept in locked file cabinets. Data entry and management procedures are described further under Quality Control and Assurance (section D. 5). FoxPRO and SAS for windows are available for data management in Malawi. Computers used in the study are protected against computer virus attack by Norton antiviral software. All data sets are backed up onto tapes on a weekly basis both at Malawi and Johns Hopkins University (JHU). For this study we propose to manage the data locally in Malawi and perform further management and data analyses at JHU in Baltimore. The data will electronically be transferred to Baltimore.

**Data analysis.** Analyses will be done using an intention to treat approach. Separate analyses for HIV infected and uninfected women will be performed and the effect of the intervention on outcomes in these two groups will be compared. The effect of the intervention will be based on comparing incidence of BV and portion of pregnancy losses between treated and untreated (control) subjects.

Multiple hypotheses will be tested in this study, requiring a diverse array of analytical methods

 Although we use the term incidence in the text, it is more accurate to define this measure as cross-sectional prevalence because the number of BV cases during a 3 month interval are a combination of new and continuing cases (due to incomplete cure and recurrences).

to compare the treatment and control arms. Descriptive comparisons will be made between the two study groups to identify potential confounding variables which could bias hypothesis testing through direct comparisons. When possible, as differences are noted, multivariate adjustment methods will be used to minimize the effect of confounders on testing the hypotheses. Continuous variables will be tested for skewness, kurtosis and outliers which could cause imprecision in standard asymptotic statistical methods. When such conditions occur, transformations such as logarithms, dichotomization or Winsorizing will be used, or nonparametric statistical methods will be implemented. For the statistical tests described below, both P-values and confidence intervals will be calculated for the parameters of interest.

Most outcomes of interest (e.g., presence of BV) are uncensored binary or categorical events. These include demographic and specific behavioral factors, etc. Contingency ( $n \times 2$ ) tables will be used to compare these events between the two study arms. Adjustment for covariates will be made with logistic or ordinal logistic regression. Comparison of binary events between two time-points within the same group will be done using methods that match on the same individual such as discordant pairs or conditional logistic regression.

In other outcomes of interest which are continuous comparison of mean values will be made using t-tests. Adjustments for covariates will be performed through linear regressions. Comparisons of continuous covariates for the same individuals in a group over different time periods will be made using paired z-tests and linear regressions on differences of values.

Some outcomes will be censored binary events. Standard survival analysis techniques such as Kaplan-Meier curves and Poisson regression will be used to directly compare outcome in both groups. These methods can also compare incidence rates within the same group over different time periods. Multivariate analogues that utilize covariates (proportional hazards models and Poisson regression) will adjust these comparisons for other covariates (57).

For some analyses we will pool repeated measurements from the same individual over multiple study visits. For example, occurrence of BV across all post-intervention study visits will be compared between study groups. For these analyses, generalized estimation equation models, which use an individual as cluster unit, will be fit to obtain robust covariance. For binary outcomes, a logit link will be used.

Data monitoring and reporting. This trial will be monitored by a Data and Safety Monitoring Board (DSMB). Formal interim analyses of efficacy of the intervention, based on the primary endpoints, will then be performed at approximately six month intervals during the projected study duration. Recommendations for early termination of positive or negative results will be guided by the symmetric group sequential O'Brien-Fleming Boundary (58). The O'Brien-Fleming design allows for early termination if extreme initial results are seen, while essentially allowing employment of the standard single stage one-sided 0.025-level test statistic at the final analysis if it is reached. This enables one to maintain the power of the single-stage design in the presence of interim monitoring without having to increase the maximum sample size. As has been the plan for other clinical trials conducted by our research team in Malawi, we will arrange for regular dissemination of information.

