**Enrollment postnatally (~6 months)**

X-----X

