**Follow-up (~18 months)**

X-----X

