#### 12.7 Data monitoring

This trial is monitored by a local Data and Safety Monitoring Board (DSMB). The members of the DSMB have no vested interest in this study. An initial administrative/safety analysis will be performed after the first three months of accrual. This will be followed by formal analyses of safety and efficacy of the intervention, based on the primary endpoints. Rates of accrual, retention, adherence and adverse events will be closely monitored and presented to the DSMB.

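### Under the planned O'Brien-Fleming looks, a final test at the single-stage one-sided 0.025 holds that level only approximately (about 0.026 to 0.029 overall), and the overall alpha it refers to is itself not settled

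*Protocol*

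**What the plan says.** Under the data monitoring heading of D.4, the protocol says that formal interim analyses of efficacy, based on the primary endpoints, "will then be performed at approximately six month intervals during the projected study duration". Recommendations on early termination are to be guided by a symmetric O'Brien-Fleming boundary. The next sentence describes the design as permitting a stop on extreme early results while "essentially allowing employment of the standard single stage one-sided 0.025-level test statistic at the final analysis if it is reached". The protocol adds that single-stage power is thereby kept with no larger maximum sample.

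Three other places bear on this:

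- D.4, sample size and power, and section 12.4.1 of the manual of operations: "hypotheses will be tested using a one-sided type 1 error of" 0.05.
- D.7, timeline: about 6 months of enrollment and about 18 months of follow-up.
- Manual section 12.7: after an early administrative and safety analysis, "This will be followed by formal analyses of safety and efficacy of the intervention, based on the primary endpoints". This section names no boundary, interval or final level.

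**The concern.** An O'Brien-Fleming boundary spends a little of the error at each interim look, so its last critical value is stricter than the single-stage one. D.4 names the single-stage 0.025 as what is essentially available at the end, and it is the only final threshold in the document. If the analyst takes that sentence literally and compares the final statistic with 1.96, the overall one-sided error is above 0.025. The reference level is also unclear, because the same section sets the type I error at one-sided 0.05. The final decision threshold and the error rate it is meant to protect should agree, and a reader cannot confirm this from the text.

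**Working it through.** **Inputs.** One-sided 0.025 at the final analysis, and looks about every six months (D.4, data monitoring). About 18 months of follow-up (D.7). One-sided 0.05 (D.4, sample size; manual 12.4.1). Powers from Tables 11 and 12, by Fisher's exact test. Looks at 6, 12 and 18 months, that is K = 3, are an inference; D.4 does not state the number.

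**1. Which alpha do the plan's own powers use?** Exact one-sided Fisher power, taking 33% as either 0.33 or one third:

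| n per arm, control rate, reduction | Stated | At 0.025 | At 0.05 |
|---|---|---|---|
| 375, 0.30, 33% | 0.87 | 0.865-0.872 | 0.921-0.926 |
| 300, 0.20, 33% | 0.54 | 0.543-0.553 | 0.662-0.671 |
| 300, 0.30, 33% | 0.78 | 0.775-0.784 | 0.858-0.865 |
| 300, 0.20, 50% | 0.91 | 0.920 | 0.957 |
| 300, 0.30, 50% | 0.99 | 0.992 | 0.997 |

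The stated powers match 0.025 to within about a point. At 0.05 all but the last are clearly different.

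**2. The boundary.** With information fractions t_k, the O'Brien-Fleming critical values are z_k = c/√t_k. The constant c is chosen so that P(Z_k ≥ z_k for some k) equals alpha under the null, with corr(Z_j, Z_k) = √(t_j/t_k) for j < k. For K = 3 equal steps and alpha = 0.025, c = 2.004. The values are 2.004/√(1/3) = 3.471, 2.004/√(2/3) = 2.454, and 2.004. The final one-sided level is 0.0225.

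**3. Error if 1.96 replaces the last value.** The overall error is then 0.025 plus the probability of crossing an interim value and afterwards falling below 1.96 at the end. That extra term is positive for any schedule with an interim efficacy stop, so the direction does not depend on K.

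| Equal looks | Boundary's final z | Its one-sided level | Overall error with 1.96 at the end | Ratio to 0.025 |
|---|---|---|---|---|
| 2 | 1.977 | 0.0240 | 0.0260 | 1.04 |
| 3 | 2.004 | 0.0225 | 0.0273 | 1.09 |
| 4 | 2.024 | 0.0215 | 0.0281 | 1.12 |
| 5 | 2.040 | 0.0207 | 0.0287 | 1.15 |

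**4. Unequal information.** For three looks with fractions assumed between 0.10/0.55/1 and 0.25/0.75/1, the final level is 0.0236 to 0.0219 and the overall error with 1.96 is 0.0264 to 0.0277. As one example, assume uniform 6-month accrual and count only the quarterly BV readings at 3, 6, 9 and 12 months after enrollment. The fractions at months 6, 12 and 18 are then 0.5/4 = 0.125, 2.5/4 = 0.625 and 1. The scaled boundary ends at z = 1.996 (p = 0.0230). Using the equal-step values 3.471, 2.454 and 2.004 at those fractions gives 0.0255. A fixed 2.004 is therefore not a safe substitute unless the steps really are equal.

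**5. Against one-sided 0.05.** The 0.0273 is below 0.05. The three-look boundary at overall 0.05 ends at z = 1.710, level 0.0437. So 0.025 is not the boundary's final level under either alpha.

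**6. Power cost.** With the drift that gives single-stage power 0.87 at 0.025 (1.960 + 1.126 = 3.086), the exact three-look boundary gives 0.8645.

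**The case against.** The strongest reply is that D.4 says *essentially*. It offers an approximation, and a gap of 0.0025 in the final level, or about 0.002 in overall error, is what such a word normally covers. The operative rule is the boundary, which carries its own final value; the sentence about 0.025 explains why the design was chosen. The companion claim about power holds to about half a point. All of this stands, and it is why the point is minor. It does not make the sentence a good statement of the final threshold, because no other threshold is given.

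Three stronger readings might be inferred, and the documents do not support them.

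- *The plan's own schedule implies 0.0225.* D.4 fixes neither the number of looks nor the information at each; 0.0225 needs three equal steps. The fractions in step 4 leave out the test-of-cure visits one month after each course (manual 3.2.1), at which BV tests are also done. Counting them under the same accrual gives about 0.21/0.71/1. Repeated readings in one woman are also correlated, so the share of readings is not the share of information.
- *The trial's intended error rate is exceeded.* This is true only against 0.025. Against the stated one-sided 0.05 it is not.
- *An early-visit BV comparison could be non-significant at month 12 and significant at month 18 on the same data.* The interim values guide early stopping and do not declare an endpoint non-significant. D.4 also does not say that visit-specific tests are the statistics monitored.

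**Conclusion.** The point holds as a minor imprecision joined to an unresolved alpha. Taken literally, a final test at 1.96 after O'Brien-Fleming interim looks has an overall one-sided error of about 0.026 to 0.029, that is 4% to 15% above 0.025, for two to five equal looks. The central figure of 0.0273 assumes three equal looks. The conclusion that 0.025 is exceeded assumes only that at least one interim look can stop for efficacy and that 0.025 is the overall level meant. The power tables favor 0.025 as the level meant, but the text says 0.05 in two places, so the documents do not settle it. This is not a serious inflation of error, and it does not threaten the trial's conclusions.

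**What to change.** In D.4:

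1. State one overall one-sided alpha, 0.025 or 0.05, and use it in the sample size text, the power tables and the monitoring text. Carry the same figure into manual section 12.4.1. If 0.025 is chosen, the stated powers can stay.
2. Replace the wording about the standard single-stage 0.025 test with the boundary's own final critical value, computed for the looks and information actually used. For three equal looks at overall 0.025 this is z = 2.004, p = 0.0225; that pair should not be fixed in advance if the steps may be unequal.
3. One convenient way is an O'Brien-Fleming-type spending function applied to a single BV statistic that accumulates over visits, such as the pooled GEE effect already planned in D.4. Other ways of computing the boundary would serve.

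Manual section 12.7 contains no conflicting level and needs at most a reference to D.4. The cost is a few sentences, a slightly stricter final threshold and about half a percentage point of power (0.870 to about 0.865 with three equal looks). No additional participants are needed.

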#### **D. 5. QUALITY CONTROL AND ASSURANCE**

Data management. Data entry programs are written on FoxPRO. The programs check out-of-range errors, skip pattern errors and verification errors before updating the master file. Further checking is done during data cleaning after data entry. Initially, checking of errors starts in the clinic where the forms are completed. A designated clerk reviews forms for incompleteness, inaccuracies and inconsistencies before the forms are sent for data entry. For quality control purposes, this clerk logs

the identification code on forms found with an error, interviewer's code, error type, form title and the specific question where the error was encountered. This monitoring is used to retrain interviewers who consistently make mistakes. At the data entry site in the office, forms are coded for missing data, not-applicable and open ended responses. During this process of coding, checking for errors continues. Written management guidelines are kept by the Data Managers in Malawi and at JHU in Baltimore.

Laboratory. The Johns Hopkins University-College of Medicine Research Project has a local laboratory capable of performing all conventional bacteriologic, hematologic and parasitologic tests. It also has a flowcytometry lab, and efforts are underway to establish a local PCR laboratory. We will use this laboratory in the proposed study. Adequate space is available for additional equipment and personnel. Strict safety and good clinical practice procedures will be followed in the laboratory. These regulations will be reinforced and supervised by the Field Director and the Project Coordinators on daily basis. Standard equipment will be used. Currently the Johns Hopkins Project in Blantyre performs routine maintenance through service contract with international agents. A quality assurance program has been developed for the local laboratory in Malawi. All tests are carried out according to written protocols. These protocols (e.g., HIV testing) follow the manufacturers recommendations and explicitly specify how to interpret the test results, and when to repeat a test if certain cut-offs points are not met. Selected specimens are tested in duplicate, at the Project laboratory in Blantyre and at the Johns Hopkins School of Hygiene and Public Health laboratories in Baltimore. Occasionally, an expatriate technician has visited the Project laboratory in Blantyre for purposes of re-training the technicians or introducing a new laboratory technique. Training sessions for technicians are regularly conducted with the start of any new study protocol, especially for unconventional tests.

#### **D. 6. STRENGTHS AND LIMITATIONS OF THE PROPOSAL**

A major strength of the proposed research is our familiarity with the site and available expertise and infrastructure in Malawi and at Johns Hopkins University in the U.S. We have extensively studied and documented bacterial vaginosis and STDs among Malawian women. We will use an appropriate design to determine the effect of the intervention - the intravaginal gel. This study will utilize the infra-structure and populations available for on-going screening activities to investigate an important maternal health problem. A potential limitation is inability of this study to adequately assess the effect of the intervention on reducing early pregnancy losses if these events are rare (e.g., 20% or less).

An aspect of this study which we will consider in our analysis is the potential reduction of HIV acquisition that can be associated with use of the active product. Our previous observational cohort studies among postnatal Malawian women have shown that BV is associated with increased acquisition of HIV. Therefore, this study could provide preliminary data to show if there is a trend of decrease in HIV seroconversion among women using the active gel compared with women using placebo. The study is not adequately powered to answer this question; nonetheless, detection of a trend can be the basis to justify a larger study.

This study could also provide preliminary data on reduction of *T. vaginalis* infections since metronidazole can treat this infection as well. This topical regimen (Metrogel), we realize, is unlikely to have a high efficacy against *T. vaginalis* compared with oral metronidazole since therapeutic levels in the urethra and perivaginal glands will not be achieved. However, reduction of genitourinary symptoms will be a desirable outcome.

